### Further measures

#### Treatment credibility and expectancy

Credibility of and expectancy of benefit from the digital CBT intervention will be assessed using the six-item Credibility/Expectancy Questionnaire [50] administered at baseline only. This questionnaire has been found to have good internal consistency and test–retest reliability [50].

#### Treatment satisfaction

Treatment satisfaction will be assessed in participants randomised to the intervention arm by the following questions administered at post-intervention: 1) “How would you rate your overall satisfaction with the programme?” (ranging from 0 (totally dissatisfied) to 10 (totally satisfied)); 2) “What could be better about this treatment programme?”; 3) “What did you like and enjoy about the treatment programme?”; 4) “In what ways did the treatment programme help you to reduce your anxiety?”; 5) “At any point during the treatment programme did you consider stopping using it? When and Why?”; and 6) “Was the content of the treatment programme specific enough to your needs?”

#### Assessment of safety

We will record the occurrence of any serious adverse events or adverse events reported to the trial coordinator at any point from study entry until the participant has left the study. A serious adverse event is defined as any untoward medical occurrence that is believed by the investigators to be causally related to digital CBT and results in any of the following: life-threatening condition (that is, immediate risk of death); or severe or permanent disability, prolonged hospitalisation, or a significant hazard as determined by the trial management committee. The study will monitor for potential adverse effects through frequent Anxiety and Depression symptom questionnaires (GAD-7 and PHQ-9). A modified symptom checklist [51] will also be used to document potential somatic and psychological side effects. The questionnaire is administered at post-intervention only and asks participants to indicate whether or not they experienced any of 14 pre-specified unwanted symptoms (e.g. low mood, feeling agitated) or other non-listed unwanted symptoms at any point during the treatment period. The original version of the symptom checklist asks participants to report on the development of any unwanted symptoms while taking part in a programme. In order to ensure that the questionnaire is also applicable to the waitlist condition (who will not have access to the programme until 10 weeks after randomisation), the questionnaire was modified after recruitment start to ask whether or not participants developed any unwanted symptoms more generally over the last 6 weeks. The questionnaire also asks to what extent any unwanted symptoms interfered with everyday functioning using a five-point Likert scale from 0 (“not at all”) to 4 (“very much”).

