The current protocol is for a parallel-group superiority RCT examining the initial efficacy of a novel digital CBT intervention for GAD compared to a waitlist control for adults with at least moderate GAD symptom severity. The digital CBT intervention, Daylight, is fully automated (i.e. standalone functioning without human input) and is delivered entirely via a smartphone application (app). This form of digital CBT takes advantage of the wide uptake of smartphone devices and offers the fewest barriers to accessibility and greatest potential for scalability [20]. A waitlist control group comparison is appropriate to test the efficacy and safety of this new intervention in this population [30].

The primary objective is to evaluate the initial efficacy of a smartphone digital CBT intervention compared to waitlist control on self-reported GAD symptom severity at post-intervention (6 weeks from randomisation). Secondary objectives are to examine the effects compared to a waitlist control on GAD symptoms at follow-up (10 weeks from randomisation), and to examine effects on the following secondary outcomes at both post-intervention and follow-up: 1) worry; 2) depressive symptoms; 3) wellbeing; 4) participant-specific quality of life; and 5) sleep difficulty.

The primary hypothesis is that smartphone digital CBT intervention will be significantly more effective than waitlist control at treating GAD symptoms at post-intervention (6 weeks from randomisation). The secondary hypotheses are: 1) digital CBT will be significantly more effective than waitlist at improving GAD symptoms at follow-up (10 weeks from randomisation); 2) digital CBT will be significantly more effective than waitlist at improving the following outcomes at post-intervention (6 weeks from randomisation): worry, depressive symptoms, wellbeing, quality of life, and sleep difficulty; and 3) digital CBT will be significantly more effective than waitlist at improving the following outcomes at follow-up (10 weeks from randomisation): worry, depressive symptoms, wellbeing, quality of life, and sleep difficulty.

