### Assessment points

Online assessments for the core study period will occur at 0 (baseline), 3 (mid-intervention), 6 (post-intervention) and 10 weeks (follow-up) from randomisation. Waitlist control participants will receive access to the digital CBT app after the follow-up assessment point (after 10 weeks from randomisation). In order to understand if effects persist over time, participants randomised to the intervention arm will also be invited to complete an optional longer-term uncontrolled assessment online at 6 months from randomisation without compensation. Table 1 presents details of the self-reported measures administered at each assessment point. After randomisation, participants will have up to 2 weeks to complete each questionnaire assessment battery. The trial coordinator will make every reasonable effort to follow the participant for the entire study period (from consent to the final follow-up assessment) using both email and telephone calls. To promote outcome data completeness, where necessary participants will be reminded to complete assessments first by a daily email reminder for up to 3 days and then by telephone for each overdue assessment. Participants who do not complete a study assessment will not be withdrawn from the study and will continue to be asked to complete any subsequent assessments. All online surveys will be hosted and stored on Qualtrics. Potential errors with data entry will be minimised as data will be entered by participants online.

**Table 1 Tab1:** Administered self-report measures and timeline

Measure	Screen	Study period			
		Baseline (week 0) and randomisation	Mid-intervention (week 3)	Post-intervention (week 6)	Follow-up (week 10)^**a**^
Basic screening questions (age, pregnancy)	X				
Medical and psychiatric history questions	X				
Prescription medication use	X				
MINI for GAD	X				
GAD-7	X		X	X	X
Demographic questions		X			
Credibility/expectancy questionnaire		X			
PHQ-9		X	X	X	X
PSWQ		X	X	X	X
SCI-8		X	X	X	X
WEMWBS		X		X	X
Patient-Generated Index		X		X	X
Modified symptom checklist				X	
Treatment satisfaction questions^b^				X	
Concomitant treatment		X	X	X	X

*GAD* generalised anxiety disorder, *GAD-7* seven-item Generalised Anxiety Disorder questionnaire, *MINI* Mini-International Neuropsychiatric Interview, *PHQ-9* nine-item Patient Health Questionnaire, *PSWQ* Penn State Worry Questionnaire, *SCI-8* eight-item Sleep Condition Indicator, *WEMWBS* Warwick–Edinburgh Mental Wellbeing Scale

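### The serious adverse event definition requires causality to digital CBT, so serious-event counts are not comparable between arms in the 10-week controlled period; death is also not named among the outcomes

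*Protocol article*

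**What the plan says.** All references are to the protocol article.

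- **Definition (Assessment of safety).** A serious adverse event is "any untoward medical occurrence that is believed by the investigators to be causally related to digital CBT and results in any of the following". The list opens with life-threatening conditions, explained as those where death is an immediate risk. What remains on the list is "severe or permanent disability, prolonged hospitalisation, or a significant hazard as determined by the trial management committee".
- **Recording (Assessment of safety).** The rule is: "We will record the occurrence of any serious adverse events or adverse events reported to the trial coordinator at any point from study entry". The window closes when a person exits the trial. No causality condition is stated for plain adverse events.
- **Waitlist exposure (Assessment points).** "Waitlist control participants will receive access to the digital CBT app after the follow-up assessment point (after 10 weeks from randomisation"). The Procedure section and Assessment of safety say the same.
- **Purpose of the control (Background).** "A waitlist control group comparison is appropriate to test the efficacy and safety of this new intervention in this population".
- **Symptom checklist (Assessment of safety).** This was reworded after recruitment began: "In order to ensure that the questionnaire is also applicable to the waitlist condition". It now asks about unwanted symptoms in general over the last 6 weeks.
- **Blinding.** The trial coordinator knows the allocation because they monitor app downloads. The rest of the research team is to be blind.

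**The concern.** Whether an event is serious and whether the intervention caused it are separate questions, and the definition answers them together. This has three consequences.

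First, a participant who cannot use the app cannot have an event caused by it. The waitlist arm therefore shows no serious events in the controlled period, whatever happens to its members.

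Second, in the intervention arm the count depends on case-by-case attribution. A true excess of serious events that is judged unrelated one event at a time would not appear among the serious events. Randomisation normally protects against this, because total events can be compared by arm without anyone having to judge cause. The definition gives up that protection.

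Third, the rule asks investigators to attribute events to the app although most of them are meant not to know who has it.

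A reader who sees no serious events on the waitlist could take that as a background rate, when it is produced by the definition. The absence of death from the list adds a gap in wording.

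**Working it through.** The protocol states no serious-event rate and no safety calculation, so there is no figure to reproduce. The check is a reading of the sections together, with a small illustration.

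**1. Structure of the definition.** An event is serious only if (A) investigators believe digital CBT caused it and (B) it leads to a listed outcome. Both must hold.

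**2. Waitlist arm.** These are participants "who will not have access to the programme until 10 weeks after randomisation". With no exposure, A is false for every event up to week 10. The serious-event count is 0 for any true rate. After week 10 the waitlist receives the app, so the zero applies to the controlled period only.

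**3. Intervention arm.** Let *r* be the true proportion of participants with an event meeting B, and *f* the share of those events attributed to the app. With 121 per arm (Sample size):

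- expected events meeting B = 121 × *r*
- expected events classed as serious, digital CBT = 121 × *r* × *f*
- expected events classed as serious, waitlist = 0

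The values of *r* and *f* below are assumptions; the documents give none. The true rate is the same in both arms.

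| *r* | Events meeting B, each arm | Classed serious, digital CBT, *f* = 10% | Classed serious, digital CBT, *f* = 100% | Classed serious, waitlist |
|---|---|---|---|---|
| 1% | 1.21 | 0.12 | 1.21 | 0 |
| 2% | 2.42 | 0.24 | 2.42 | 0 |
| 5% | 6.05 | 0.61 | 6.05 | 0 |

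With no true difference, the recorded difference is never below zero and depends on *f*. The reverse can also happen. If the true rate were 5% on digital CBT and 1% on waitlist, the real excess would be 6.05 − 1.21 = 4.84 events. With *f* = 10% the recorded counts would be 0.61 and 0. The recorded difference therefore does not estimate the true one in either case.

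**4. Checklist against definition.** Both stand in the same section. The checklist originally asked about symptoms while taking part in a programme, and it was changed because that did not suit the waitlist. The serious-event definition has the same feature and was left as it was.

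**5. Blinding against definition.** Relatedness to the app depends on whether the participant had the app. Investigators who are blind either have to be unblinded to classify an event or have to classify it without that fact. Events are reported to the trial coordinator, who is not blind, but the definition rests on the belief of the investigators.

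**6. Death.** It is not in the list. A fatal event could enter only through the life-threatening wording or the committee's significant-hazard category, and only if judged related to digital CBT.

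**The case against.** The strongest reply is that the definition is not the protocol's only safety measure. Plain adverse events carry no stated causality condition. The checklist was adapted so that both arms can answer it. GAD-7 and PHQ-9 are used to monitor for harm, and Table 1 restricts only the treatment satisfaction questions to the intervention arm. All of these can be compared between arms. This stands, and it rules out several stronger readings that a reader might infer:

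- *That a promised safety comparison is impossible.* The Statistical analysis section specifies no between-arm analysis of serious events, and the objectives contain no safety endpoint. The nearest text is the general sentence in Background. Other safety data remain comparable.
- *That unrelated serious events are lost.* They lose the serious label. Nothing says they go unrecorded, and they may be logged as adverse events.
- *That 0 of 121 would be reported with an upper limit of 3/121 = 2.5%.* The protocol plans no such limit, so this figure corrects nothing in it.
- *That every hospital admission should count as serious.* No section supports that demand, and a shorter admission could enter through the significant-hazard category.

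It can also be said that a condensed article leaves event forms and tabulations to the full protocol or analysis plan. That is fair for those details. The definition itself, however, is stated in the article, and it is the definition that is at fault.

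The other measures do not fully replace a serious-event count. The checklist is given once, at week 6, so it does not cover weeks 6 to 10. The symptom scales are self-completed, so a participant who has died or is incapacitated returns none. Nothing in the article says that the outcome or severity of plain adverse events is captured.

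**Conclusion.** The point holds in this limited form. For the 10-week controlled period, the stated definition fixes the waitlist serious-event count at zero and makes the intervention count depend on attribution, so the two cannot be compared. This does not fit the Background statement on testing safety, and it is in tension with the Blinding section. Death is not named, which is a gap in wording, although a related death could enter through two of the listed categories.

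The size cannot be given as a single figure, because the documents state no event rate. Under assumed rates of 1% to 5%, between about 1.2 and 6.1 waitlist events would go unclassified as serious. The conclusion rests on two assumptions: the definition is applied as written, and waitlist participants have no access to the app before week 10, as the article says. The primary outcome, sample size and efficacy analyses are not affected.

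**What to change.** 1. Define a serious adverse event by its outcome alone, identically in both arms, and name death among the outcomes.
2. Record relatedness to digital CBT in a separate field, and state who judges it and whether they know the allocation. Blinded staff can then classify seriousness in both arms.
3. Tabulate all serious events by randomised arm for the controlled period, then the related ones.
4. Reconcile the Background statement on safety, the Blinding section and Assessment of safety.

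The cost is a change of wording and one field on the event record. A few more events will be logged as serious. Trial status says recruitment was still open when the article was submitted. Events already logged as adverse events could be reclassified where the record gives enough detail of the outcome; the article does not say whether it does.

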### Sample size

The sample size calculation was conducted using G*Power 3 [31]. The study aims to recruit 242 participants with GAD, with 121 participants randomised to each arm. This recruitment target accounts for approximately 30% attrition, based on the range of dropout rates from previous RCTs comparing smartphone-based digital interventions for anxiety to waitlist (19% to 45%; [32–34]). The sample size was determined based on an estimated medium effect on post-intervention scores on the seven-item Generalised Anxiety Disorder questionnaire (GAD-7) (Cohen’s *d* = 0.50) between the digital CBT and waitlist arms, with 90% power, a 1:1 allocation ratio, and with *α* set at 0.05. The effect size is based on a recent meta-analysis of RCTs of smartphone-delivered psychological treatment for anxiety versus waitlist which demonstrated a small-to-moderate (Hedges’ *g* = 0.33) between-group post-intervention effect on anxiety symptoms when compared to any active or waitlist/inactive control condition [28]. When comparing smartphone interventions with only waitlist/inactive control conditions, Hedges’ *g* increased to 0.45. The effect size of 0.50 corresponds to a minimally clinically significant 2-point change on the GAD-7 and a standard deviation of 4 in this population [35].

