Participants will be recruited online from the UK and the USA. A number of recruitment strategies will be used, including online, print, and broadcast media advertisements. Participants will receive 10 GBP in Amazon.com gift vouchers (or USD equivalent at the time of payment) in exchange for completing each of the core assessments following baseline (mid-intervention, post-intervention, and follow-up), and a bonus of 10 GBP (or USD equivalent) in vouchers for completing all assessments. Therefore, each participant can receive up to a total maximum of 40 GBP (or USD equivalent) in vouchers. Payment will be made at the end of the core study period for each participant (after 10 weeks from randomisation). If participants withdraw from the study, payment will be made for completion of any assessments at the point of withdrawal. Participants may withdraw themselves from the study for any reason at any time. The study investigator may also withdraw participants from the study to protect their safety and/or if they are unwilling or unable to comply with required study procedures after consultation with the study investigator team.

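### The symptom checklist is offered only at week 6 with a rolling six-week recall, so people who miss week 6 but answer week 10 give no side-effect form, and late answers may omit early treatment

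*Protocol article*

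**What the plan says.** All references are to the protocol article.

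- **Schedule.** Assessment of safety states: "The questionnaire is administered at post-intervention only". Table 1 marks the checklist at week 6 and nowhere else. The same table schedules GAD-7, PHQ-9, PSWQ and SCI-8 at weeks 3, 6 and 10.
- **Period covered.** The form is described as asking about 14 listed symptoms or "other non-listed unwanted symptoms at any point during the treatment period". After recruitment had started it was reworded, so that it would also suit the waitlist arm, to ask whether participants "developed any unwanted symptoms more generally over the last 6 weeks".
- **Completion window.** Under Assessment points, "participants will have up to 2 weeks to complete each questionnaire assessment battery". The article does not say whether this window opens at the nominal week or is centred on it.
- **Missed assessments.** In the same section, people who skip an assessment "will not be withdrawn from the study and will continue to be asked to complete any subsequent assessments".
- **Other safety data.** Adverse events reported to the trial coordinator are recorded from study entry until the participant leaves, and GAD-7 and PHQ-9 are also used to watch for harm.

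**The concern.** The Background gives safety, alongside efficacy, as a reason for the waitlist comparison. The checklist is the only form that asks both arms about a list of somatic and psychological symptoms and how far they interfered with daily life. Two features of its schedule weaken it.

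First, there is no second chance to collect it. Someone who misses week 6 stays in the trial and is asked for the week-10 battery, but that battery has no checklist. Such a person can inform the efficacy analysis and is absent from the side-effect table. This is a data-collection choice; no analysis plan can recover a form that was never offered.

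Second, the recall period moves with the day of answering, while the period of interest starts at randomisation, when app access begins. The two coincide only for a form answered at week 6. A late answer drops the start of treatment, and symptoms that began and ended early can be missed.

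At stake is how complete the side-effect description is. The efficacy results do not depend on it.

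**Working it through.** **Inputs.** Sample size section: 242 participants, 121 per arm, d = 0.50 (2 points over an SD of 4), 90% power, alpha 0.05, about 30% attrition, and 19% to 45% dropout in earlier trials. Assessment of safety: one administration at week 6, six-week recall. Assessment points: up to 2 weeks per battery. Procedure: app access immediately after randomisation (week 0).

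**Step 1: the plan's own figure.** Two-sided alpha 0.05 and 90% power at d = 0.50 need 85 per arm (normal approximation) or 86 (t-test).
- 85 / 0.70 = 121.4, rounded up to 122 per arm, 244 in total.
- 86 / 0.70 = 122.9, rounded up to 123 per arm, 246 in total.
- Working back from 242: 1 − 172/242 = 28.9% attrition.

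The stated 242 is consistent with roughly 30% attrition, so that figure is usable below.

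**Step 2: upper bound on forms a week-10 catch-up could recover.** Assume the attrition allowance applies at week 6. Missing checklists per arm = 121 × attrition:

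| Attrition | Calculation | Per arm |
|---|---|---|
| 19% | 121 × 0.19 = 22.99 | 23 |
| 30% | 121 × 0.30 = 36.3 | 36 |
| 45% | 121 × 0.45 = 54.45 | 54 |

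These counts mix people who have left with people who merely skipped week 6. Only the second group can answer at week 10, and the article gives no number for it. Each figure is therefore a ceiling under its attrition rate.

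**Step 3: recall gap.** A form answered at week t covers weeks t − 6 to t. For t between 6 and 12 it omits t − 6 of the 6 intervention weeks:

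| Answered at week | Covers weeks | Intervention weeks omitted |
|---|---|---|
| 6 | 0 to 6 | 0 |
| 7 | 1 to 7 | 1 of 6 (17%) |
| 8 | 2 to 8 | 2 of 6 (33%) |

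If the 2-week window opens at week 6, the latest permitted answer is at week 8 and the largest gap is 2 weeks. If it is centred on week 6 (weeks 5 to 7), the mismatch is at most 1 week: at week 7 one treatment week is lost, and at week 5 one of the recall weeks precedes randomisation.

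**Step 4: would the present wording work on extra forms?** No.
- At week 10 it covers weeks 4 to 10 and omits 4 of the 6 intervention weeks (67%).
- At a week-3 withdrawal it covers weeks −3 to 3, so half of the recall falls before randomisation.

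Adding occasions without changing the wording would therefore not help.

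**The case against.** A single end-of-treatment checklist with the same recall in both arms is a coherent choice. At the scheduled visit the reworded item and the intended treatment period coincide, so the article does not contradict itself. The window opening and the share of late answers are unknown, the window rule is the same in both arms, and daily emails, a telephone call and vouchers all push towards timely completion. A week-8 answer still covers six weeks of app access; what it can lose is early onset. Spontaneous reports and GAD-7/PHQ-9 supply some safety data, and safety is not among the stated objectives or hypotheses. All of this stands, and it is why the point is minor.

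It does not remove the point. Spontaneous reports are not solicited, and a serious event counts only if judged causally related to digital CBT, so neither gives a like-for-like comparison of arms. GAD-7 and PHQ-9 do not cover the checklist's range of symptoms. The 6-month assessment is optional and for the intervention arm only.

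Three stronger readings are tempting and are not supported:
- A reader might infer that side-effect data will be lost for 36 people per arm because of this schedule. The basis is a planning allowance: "This recruitment target accounts for approximately 30% attrition". It would affect every week-6 outcome, including the primary one, and does not separate those who withdraw from those who skip one battery.
- A reader might take the 2-of-6-weeks gap as typical. It is the worst case for an individual who answers on the last permitted day, under one reading of the window.
- A reader might infer that harms in the app arm will be understated. The documents give nothing on how side effects relate to non-response or lateness, so the size and direction of any bias are unknown.

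**Conclusion.** The concern holds as a minor, inexpensive improvement to safety ascertainment. With one administration at week 6, anyone who misses that battery but answers at week 10 contributes efficacy data without a side-effect form. Their number is not given; it is at most about 36 of 121 per arm if 30% attrition applies at week 6 (23 to 54 over the cited range). Separately, the rolling recall can omit up to the first 2 weeks of treatment for late responders if the completion window opens at week 6, and is out by at most 1 week if the window is centred on it. On-time responders are fully covered, as are people who stop using the app but still answer at week 6. No efficacy conclusion changes.

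**What to change.** 1. **Fix the period.** Ask about symptoms 'in the 6 weeks after [randomisation date]', showing the date, and record when the form was completed. An open-ended 'since you were randomised' would give late responders a longer observation period; a fixed period gives everyone the same one.
2. **Add a catch-up.** Put the same form in the week-10 battery for people in either arm who did not complete it at week 6. The arms remain comparable: "Waitlist control participants will receive access to the digital CBT app after the follow-up assessment point". The fixed period also lies wholly before that access.
3. **Use any contact at withdrawal.** If there is such contact, offer the form then, asking about the time since randomisation. The Participants section says only that on withdrawal "payment will be made for completion of any assessments at the point of withdrawal"; it describes no exit contact, so this step cannot be counted on.
4. **Reporting.** Keep on-schedule week-6 forms as the main comparison by arm. Report catch-up forms by arm as a supplement and in a combined sensitivity summary, with the number responding and the period covered.

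**Cost.** One reworded item and one existing online form on one further occasion for some participants. Week-10 forms ask people to recall the same six weeks from further away. The trial, already running, gains a further wording version, to be reported separately from earlier ones. Recovery will be partial, since some who miss week 6 will also skip week 10.

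**Timing.** Only participants not yet assessed can benefit. Recruitment was expected to end in November 2019. If the last participant was randomised on 30 November 2019, week 10 falls on 8 February 2020 (70 days later), before the article's publication date of 23 April 2020. If collection has closed, what remains is to report the number of checklists by arm and, where completion dates are held, how many were answered after week 6.
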